## Abstract

**Background:**

Children usually refuse to eat and taste fruits and vegetables; and turning unhealthy eating habits around is an important social challenge in industrialized countries. The *Dastatuz* project aims to study children food neophobia and to enhance fruit and vegetable acceptance.

**Methods:**

A quasi-experimental, multicentre, controlled and prospective intervention study is proposed, in which early factors influencing new food acceptance will be studied. Mothers in the third trimester of pregnancy (*n* = 144) and their infants will be the study population. Experimental groups will be established based on mothers´ fruit and vegetable intake (standard or high intake) and weaning method (baby lead weaning vs spoon feeding). The project will assess the possible impact of maternal diet and complementary feeding on infants eating behaviour until 18 months of age. Outcome measures will comprise maternal diet and psychological features during pregnancy and breast-feeding (validated questionnaires). Compositional and physicochemical analysis of milk during breastfeeding will also be carried out. During weaning, until 18 months of age, children’s diet will be assessed with 24 h recalls and acceptance of new fruits and vegetables will be studied using video recording.

**Discussion:**

If the intervention is effective, this research work would have a high potential to be transferred to future public health programs or nutrition guidelines, as a feasible solution to achieve a higher intake of fruits and vegetables among children.

**Trial registration:**

This study is registered at ClinicalTrials.gov. Identifier: NCT04262102. Registration date: February 10, 2020 - Retrospectively registered.

## Background

Neophobia or new food refusal (ranging from severe rejection to a moderate manifestation) is a common behaviour in children and should be carefully considered due to the important implications on the current and future health status of the infants [1–3]. Parents, caregivers and health professionals are concerned about infant food neophobia and picky eating, since it can derive in an inadequate diet [4, 5]. The American Psychiatric Association described food neophobia as ‘avoidance and/or restriction to food based on the extreme sensitiveness to the appearance, colour, smell, texture, temperature or taste’ [6]. Hay et al. [7] described a 0,3% prevalence in the Australian population over 15 years of age and showed an association to socio-economic disadvantaged groups and obesity. Although there is limited prevalence data, it is known that clinically significant feeding and eating difficulties are common in early childhood, with estimates of 5–25% in young children [1, 8]. Neophobia has been linked to poor growth and deficient development [9, 10]. Moreover, childhood constitutes the key period in which feeding behaviour is established and then maintained up to adulthood [11, 12]. This is the reason why many authors highlight the relevance of addressing neophobic behaviour since childhood [13].

Fruits and vegetables (FV) are the main food target in infant food neophobia, because despite their relevant health contribution [14], these are the most commonly rejected foodstuffs and, consequently, they have become a health objective. Nutritional interventions and/or educational programs carried out in the past years have not succeeded to increasing FV intake further than half a portion [15]. According to the literature, fruits are more easily accepted by children than vegetables [16, 17]. There is still a compelling need for a more accurate characterisation of the children’s food consumption profile. National and local dietary surveys, such as the ENALIA Study [18] and the COSI Study [19], and unpublished data from the Vitoria-Gasteiz City Council Nutritional Observatory (2007) showed that only around 20–30% of children follow fruit intake recommendations and around 10% fulfil vegetable intake recommendations. In the view of the above mentioned data, it is plausible to think that FV intake figures will be even lower for neophobic children.

Norris, Spettigue and Katzman [20] pointed at the need for a better definition of factors affecting neophobia prevalence at different stages of life. Indeed, it would be useful to identify and characterize those early variables that might act as determinants of the neophobic behaviour prevention. There are limited prospective interventions conducted on the influence of mothers’ diet and complementary feeding at weaning on food neophobia or picky eating. One of the scarce works, a recent retrospective study based on online questionnaires, did not find any significant difference between complementary feeding method and eating behaviour or neophobia [21]. This observation opposes to the results of the intervention study carried on by Taylor et al. [22], in which an adapted baby-led weaning resulted in less food fussiness than spoon feeding. These aspects must be addressed taking into account the individual differences on food acceptance, such as caregivers eating habits, which, undoubtedly, influence food preference development in infants [17, 23].

Some authors have described a positive reaction of newborn children towards foods or substances consumed by their mothers during pregnancy or breastfeeding period [24–26]. Moreover, several studies have described lower levels of picky eating and/or food neophobia in children who have been exclusively breastfed for 6 months [27]. Some authors defend that breastfeeding itself improves acceptance of new foods, while some others consider that the variety of flavours present on the mother’s milk may constitute a key factor influencing future food acceptance [17, 27–31]. Nonetheless, there is an absence of empiric evidence to explain the causal relationship between breastfeeding and picky eating behaviour [3]. The relation between the diet and the flavour profile has been observed in mammals, but the sensory profile in human milk has only been studied recently [31, 32]. To the best of our knowledge, there is no research on the sensory profile of human milk related to the overall diet profile of the mother [29].

Regarding the weaning period, a new approach called Baby-Led Weaning (BLW), as opposed to the traditional spoon-feeding (SF), has become popular mostly in the United Kingdom and New Zealand [33]. Actually, regarding the Spanish state, a recent study carried out in Galicia shows a general estimated prevalence of BLW of 14% [34]. Although there is not a clear or precise definition, BLW can be characterized as follows: children are the ones feeding themselves, deciding which will be the rhythm and quantity of food to swallow, using their hands, ingesting pieces of food (not purée, or less than 10% of the total ingested food in purée), sharing family meals, and eating the same family-food [33, 35].

BLW has arisen some concerns on parents, caregivers and health professionals, mainly due to the chocking risk [36]. Nevertheless, some authors have reported no difference on the chocking risk between traditional weaning and BLW [37, 38]. Additionally, there is also a concern about the unfulfilment of the energy requirements of the child [33], particularly regarding initial energy intake. However, the available scientific evidence is not strong enough to support this idea [39]. Among nutrients, iron deficiency is the most generally stated worry [40]. Nonetheless, it has been demonstrated that BLW does not increase iron deficiency nor growth faltering [38]. In any case, children’s diet should be as balanced as possible, in order to fulfil all the nutritional requirements and avoid deficiencies. Some paediatricians have manifested their concern about the possible inappropriateness of food offered to the child when following BLW, stating that meals could be high in fat and too salty [39]. Moreover, allergen intake is also a subject of debate, because food selection is baby-led and this could imply less control over allergen intake in a period when children are more susceptible to food allergens [4]. However, some positive aspects have also been pointed out: usually parents following BLW fulfil WHO (World Health Organization) recommendations regarding the start of complementary feeding at 6 month of age, while SF is associated to an earlier weaning [35]. It has also been observed that when following BLW children develop a better ability for satiety responses [41], which constitutes a protection against obesity. Furthermore, BLW has been related to a greater food variety intake or acceptance [39].

Additionally to the development of FV liking and acceptance, it has been proved to be a malleable aspect [17]. Repeated exposure to certain FV or exposure variety seems to have an impact on acceptance. Maier et al. [24] also concluded that the frequency has more importance than the amount of FV offered. Experts point out that flavour/food repetition is relevant, providing a saturation limit is not exceeded [24, 28]. Finally, some factors, such as the texture, which could be important in the weaning period, remain understudied even though some authors have proved its relevance in food acceptance during the introduction of the complementary diet [42, 43].

In view of the above, and given the increasing popularity of the baby-led approach, the influence of the weaning method (traditional SF versus BLW) needs to be urgently addressed by means of a systematic methodology. Several methodological aspects should be specially considered, particularly paying attention to the food intake reports. In this regard, some authors have shown mismatching of parents/caregivers reported questionnaires and objective measurements [3, 44]. Taylor et al. [22] performed the only randomised controlled trial designed as such until now. The authors pointed out the relevance of proper and accurate information to parents about the correct dietetic approach for BLW. Along with that, a review demonstrated that educational interventions improve complementary feeding practices, including: exclusive breastfeeding duration enlargement, beginning of complementary feeding delay, offered foods adequacy and hygiene practices [45].

All the stages mentioned above (pregnancy, lactation and later caring stages of the baby) involve a huge change in women’s lives. That is why studies involving these stages should pay special attention to information and support given to families. In fact, pregnancy might be a source of stress [46], fatigue and has a negative impact on the quality of life, which might be associated to depression and anxiety [47, 48]. This period is full of expectations around birth and support given by their partners, relationship with healthcare professionals, active participation on decision making, and pain management [49]. On the other hand, the duration and exclusivity of breastfeeding has been predicted by the variable breastfeeding self-efficacy [50]. In order to persist and achieve concrete objectives it is fundamental that progenitors believe they are capable of becoming “good parents” [51]. Although the relationship between psychological health and attachment bond has vastly been studied [52, 53], investigations assessing the possible association between psychological wellbeing/perceived self-efficacy and parental stress of the mother and the decisions taken regarding the baby’s feeding remain unknown. Nonetheless, those feelings could influence the feeding modalities employed by parents, and it is becoming clear that control-based parental feeding styles affect negatively the children’s eating performance, while modelling positive eating behaviour happens to be successful [54–57].

With the aforementioned aspects in mind, we propose an intervention protocol to study the influence of the mother’s diet and the weaning method, as possible early factors, conditioning new fruit and vegetable acceptance during the period in which these foods are introduced in the child’s diet. The protocol has been designed taking into account the psychological aspects involved in the stages studied.

## Methods

### Hypothesis

A high intake and variety of FV during pregnancy and breastfeeding will lead to distinctive sensorial experiences for the baby, different from the ones whose mothers followed a “standard diet” (SD) (as described in the National Nutrition Surveys). This consumption profile will promote the acceptance of FV along complementary feeding. Additionally, a correct BLW may also contribute to establish healthy eating habits in children.

### Objectives

The main objectives of the present study are: on the one hand, to describe the possible impact of the mother’s diet during pregnancy and breastfeeding on children’s eating behaviour from weaning until 18 months of age; and, on the other hand, to study the possible effect of the weaning method (spoon-fed or baby-led) on the eating behaviour of children from weaning until 18 months of age.

This implies the following secondary objectives which are: (i) to analyse whether there is a relation between the mothers’ diet and the physicochemical characteristics of human milk, (ii) to study the possible relation between the mothers’ diet patterns and the chosen weaning style, (iii) to examine the relationship between the mothers’ psychological well-being, self-efficacy, parental stress and decision making regarding the child’s feeding, (iv) to characterise the BLW diet versus the SF diet regarding nutrient intake and main health indicators of children during the first 18 months of age, and (v) to carry out a risk assessment of potential food allergen intake associated to the BLW diet versus the SF diet.

### Participants

Women will be selected through the midwife consultation from the Basque Primary Healthcare Units (Northern Spain) on the second trimester of pregnancy attending routine control consultations. Midwifes will offer information regarding the project to the future mothers who then can directly contact the researchers in case they are willing to participate in the study.

The inclusion criteria will be: healthy mothers (aged between 18 and 45 years) who are notified about the study (and express interest to participate) before week 24 of gestation; who could be Basque, Spanish or English speakers and will live in the Basque Country until the child will be 18 months old. The exclusion criteria include unhealthy mothers or complicated pregnancies (all types of diabetes mellitus, high blood pressure, etc.), those not willing to breastfeed, mothers with extreme diet restrictions and those with severe non-adherence to prescribed diets. Additionally, any conditions that may be contraindicated for the development of the project will also be excluded (i.e. post partum complications, diseases). After birth, women will be excluded if their infant is born before 37 weeks of gestation; or if a congenital abnormality, physical condition, or intellectual disability, which might affect the infant’s feeding or growth is identified. Finally, milk will not be collected from those breastfeeding mothers who are taking any medication, which might alter significantly milk composition.

### Sample size

Sample size (*n* = 144) has been estimated taking into account main variable: FV intake achievement (proportion of children who reach recommendations). Accepting an alpha risk of 0.05 and a beta risk of 0.2 in a bilateral contrast, 72 subjects in the first group and 72 in the second are required to detect as statistically significant the difference between the proportion of children who reach recommendations, which for the control group is expected to be 25% and for the treatment group 50%. The final sample size has been increased by 20% in order to accommodate a drop out of 20%.

### Allocation to groups

Assignment to the control or treatment groups will be conducted according to mothers likings, type of diet and willingness to perform the weaning process traditionally (SF) or following a baby-led approach (see Table 1). Group assignment will be blind for participants.

**Table 1 Tab1:** Distribution of the control (Ctrl) and intervention (I) groups

Groups	Mothers´ diet during last trimester of pregnancy and breastfeeding	Weaning approach	Group codes
1	“Standard” diet as described in National Diet Surveys (Ctrl)	Spoon feeding (Ctrl)	SD_SF
2		Baby-led (I)	SD_BLW
3	High Fruit and vegetable intake (I)	Spoon feeding (Ctrl)	HFV_SF
4		Baby-led (I)	HFV_BLW

*SD* standard diet; *SF* spoon-feeding; *BLW* Baby-Led Weaning; *HFV* high fruit and vegetable

#### Intervention group

Baseline questionnaires and initial dietary assessment will be the base for group assignment. Once participants are matched to a group, they will be given a code and will be anonymously treated thereafter. Those above the national (Spain) mean consumption of fruits and vegetables (about 414 g/person/day [58]) will be included in the intervention group. During the study, participants will be encouraged and assessed to achieve even a higher FV intake, following the recommendations given by Aune and colleagues of 800 g/person/day [14]. If a significant decrease in FV intake is detected in the participants' diet during the follow-up visits, dietetic assessment will be performed in order to restore the initial intake. With regard to the weaning groups, those better disposed to follow a baby-led approach will be included in the intervention group.

#### Control group

Baseline questionnaires and initial dietary assessment will be the base for group assignment and the study participants assigned to the control group will receive the same anonymous treatment as those in the intervention group. Those below the national (Spain) mean consumption of fruits and vegetables (about 414 g/person/day) or/and those who claim to have difficulties achieving the recommended portions will be included in the control group. When a fruit consumption of one standard deviation below the mean is detected, dietetic assessment will be performed in order to encourage, at least, the mean intake. As for the weaning groups, those better disposed to follow a spoon-feeding approach will be included in the control group.

### Study procedure

Regardless of the group assignment, all participants will receive the current standard recommendations and care. Dietetic guidelines will be explained at the beginning of the study (last trimester of gestation) and after birth to ensure breastfeeding requirements. Intervention groups will receive additional diet recommendations so that they keep to the high fruit and vegetable consumption and to assure safety and a balanced diet along complementary feeding by BLW. The follow-up for the control group will be focused on ensuring a standard fruit and vegetable consumption and reinforcing general dietetic guidelines. Diets of mothers and children will be closely reviewed during the study to prevent deterioration. This implies a time lapse from the third trimester of the pregnancy until children are 18 months old. Follow-up, measurements will be performed on 6th–7th months of pregnancy, before delivery; on the 2nd, 4th, 6th, 12th and 18th months from birth. Figure 1 summarises the study outline.

**Fig. 1 Fig1:**
[figure not shown]
Timeline of the *Dastatuz* project. Legend: Main stages: 3rd trimester of pregnancy, breastfeeding and weaning and complementary feeding until the children are 18 months old. Q1, Q2, Q3, Q4, Q4’and Q4´´ refer to online questionnaires in each stage

Participants will receive information in 5–6 sessions throughout the study (with an approximate duration of 20–40 min) which will be delivered by a dietician-nutritionist. These meetings were planned to be held face to face, but they were adapted to online format due to the measures adopted within the COVID19 pandemic. Informative sessions will be either individual or group meetings (always considering participants allocation group) since the dates allocated for the sessions will depend on each participant’s delivery date: before the 3rd trimester of pregnancy, 1 month before the delivery date, and 4 months, 6 months, 12 months and 18 months after the delivery date. The topics that will be addressed in these meetings include: healthy eating, breastfeeding, complementary feeding, balanced diet, dietetic recommendations, technical aspects regarding completion of questionnaires, and signing of the informed consents. Additionally, instructions on different study procedures will also be given (e.g. milk extraction, child observation).

### Outcomes

#### Primary outcomes

Change of fruit and vegetable intake: measured by an ad hoc questionnaire reported by parents. At the beginning of the weaning process (depends upon each participant, 4th–6th month) and on the 12th and 18th month after delivery. Prior to the paediatric consultation date, each family will record during 24 h the food intake of the child indicating: the specific food consumed and its composition or commercial brand if necessary; the cooking method; and weight of the food consumed. Three days will be randomly selected within a week, ensuring that two of them are week days and one of them is a weekend day in order to avoid the “day” effect. Families will be provided with informative material on how to perform the measurements and record the information, together with blank forms they need to complete.Change of food acceptance to the exposed FV as the measurement of willingness to eat them: assessed by direct observations of child behaviour (see Fig. 2) and ad hoc questionnaires. Some days after the paediatric control visits on the 6th, 12th and 18th months parents will be contacted by telephone to gather information about foods which might be new for the child and have never been tried before. Any doubts arising on diet or possible recipes are clarified. Parents will be asked to record a video of these mealtimes and send them to the research team. Researchers will explain the video-recording protocol so that it is always recorded following a standard procedure. The Feeding Infants: Behaviour and Facial Expression Coding System (FIBFECS) [59] will be taken into consideration for the analysis of the video recordings. Swallowing times and acceptance or rejection signs will be taken as the main parameters.

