
### Statistical analysis

#### Quantitative data

The initial analysis of data will be performed on an *intention to treat* basis. A baseline descriptive analysis of the sociodemographic data and measured predictive variables will be carried out to ensure comparability between the intervention and control groups (mothers in the first phase and children in the second phase). Intra-group and inter-group differences in main continuous variables will be analysed by Student’s t test or non-parametric tests (Wilcoxon signed-rank test and Mann–Whitney U test) at different measurement times. For qualitative variables, comparisons will be made using Pearson’s chi square test.

Linear mixed-effects models with participant-level random intercepts will be used to study the effectiveness of the intervention and we will consider adjusting for any demographic or predictive variable results that show important differences at baseline. All statistical analyses will be conducted using the STATA 14.0 and IBM-SPSS 24.0 software. Confidence intervals of 95% and the significance level (*p* values) will be reported.

Subsequent to the initial analysis, we will also carry out a *per protocol* analysis in order to identify possible differences to the intention to treat analysis, which may occur as a result of a differential compliance of participants with the research protocol.

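### The primary outcome is labelled a change in the child's fruit and vegetable intake, but its first record is taken after exposure, at an unfixed age, and is not a valid baseline for either contrast

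*Protocol article*

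**What the plan says.** The Primary outcomes section opens with "Change of fruit and vegetable intake: measured by an ad hoc questionnaire reported by parents". The child's intake is recorded "At the beginning of the weaning process (depends upon each participant, 4th–6th month) and on the 12th and 18th month after delivery". These are the only child intake records.

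The maternal-diet factor in Table 1 (Allocation to groups) is the mother's "diet during last trimester of pregnancy and breastfeeding". The Hypothesis section says of a high and varied FV intake: "This consumption profile will promote the acceptance of FV along complementary feeding".

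The Sample size section uses a different variable, "FV intake achievement (proportion of children who reach recommendations"), with 25% expected in the control group and 50% in the treatment group.

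The Quantitative data section says "Intra-group and inter-group differences in main continuous variables will be analysed by" t tests or rank tests at the different measurement times. It assigns effectiveness to linear mixed models with a random intercept per participant. It also plans a baseline comparability check, for mothers in the first phase and children in the second, and will consider adjusting for variables that differ materially at baseline.

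**The concern.** A change outcome needs a reference value that the exposure could not yet have affected. Here the only candidate is the start-of-weaning record.

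For maternal diet, that record comes after the last trimester and after most of the breastfeeding period. Any early benefit of the mother's diet would already be in it, and subtracting it would remove that benefit from the estimate. Adjusting for it as a child-phase baseline variable could remove part of the effect in the same way.

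For weaning, the record is taken when the method is already in use, at an age that depends on the family. The Background notes that parents using baby-led weaning (BLW) usually start at 6 months, "while SF is associated to an earlier weaning" (SF being spoon-feeding). A change from that record may therefore cover a different age span in each weaning group.

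At stake is whether the named primary outcome measures the effect in the hypothesis, and whether it is the quantity for which the trial was sized.

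**Working it through.** **1. What the trial was sized for.** Inputs from Sample size: 25% against 50%, two-sided alpha 0.05, power 0.80, equal groups, 20% dropout. With the pooled-variance formula, mean proportion 0.375 and difference 0.25:

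n = [1.96·√(2·0.375·0.625) + 0.8416·√(0.25·0.75 + 0.50·0.50)]² / 0.25² = 57.67 per group.

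Dividing by (1 − 0.2) gives 57.67/0.8 = 72.09, which agrees with the stated 72 per group. The figure is sound for a comparison of attainment proportions. It says nothing about a change in intake.

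**2. Length of the change interval.** From the stated record times:

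| First record | Span to month 12 | Span to month 18 |
|---|---|---|
| Month 4 | 12 − 4 = 8 months | 18 − 4 = 14 months |
| Month 6 | 12 − 6 = 6 months | 18 − 6 = 12 months |

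The longest span exceeds the shortest by 8/6 − 1 = 33% at month 12 and by 14/12 − 1 = 17% at month 18. The acceptance outcome in the same section uses fixed ages (6, 12 and 18 months), so fixed ages are workable in this trial.

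**3. Maternal-diet contrast under a literal change.** Let D be the group difference at month 18 and f the share of it already present at the first record. The change contrast is D − fD = D(1 − f). For an illustrative D of 0.5 SD:

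| f | 0 | 0.25 | 0.5 | 0.75 | 1 |
|---|---|---|---|---|---|
| Change contrast (SD) | 0.50 | 0.375 | 0.25 | 0.125 | 0 |

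**4. What that does to power.** The documents give no SD, correlation or early effect, so these are assumptions: 58 per group, D = 0.53 SD, the same SD at both times, within-child correlation ρ. The SD of change is √(2(1 − ρ)). Power is Φ(D(1 − f)·√(58/2)/SD − 1.96), and comparing month-18 levels uses SD = 1 and f = 0.

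| f | Change, ρ = 0.3 | Change, ρ = 0.5 | Change, ρ = 0.7 | Month-18 level |
|---|---|---|---|---|
| 0 | 67% | 81% | 96% | 81% |
| 0.25 | 44% | 57% | 79% | 81% |
| 0.5 | 23% | 30% | 45% | 81% |
| 0.75 | 9% | 11% | 15% | 81% |
| 1 | 2.5% | 2.5% | 2.5% | 81% |

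The 2.5% in the last row is the chance of a significant result in the expected direction when the contrast is zero.

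**5. What the planned model would estimate.** A mixed model fitted to all three records can report the group difference at months 12 and 18, which is a level. It can also report the group-by-time interaction relative to the first record, which is a change. The article does not say which one carries the effectiveness claim, and the outcome label points to the second. The within-group tests are tests of change. Infants move from milk to solid food over this period, so these tests will reflect age in every group.

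**The case against.** The strongest reply is that the article never commits to a change score. It gives no formula, does not call the first record a baseline, and plans tests at each time plus a mixed model, both of which can compare levels. The same change wording also heads food acceptance and maternal diet, so it may be only a generic label for repeated measures. This stands, and it makes the bias conditional. It does not clear the label: the article itself names the primary outcome and its record times, and read as written they give a change with no pre-exposure reference.

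The second reply is that attenuation of the maternal-diet contrast needs a group difference at the first record. If intake is almost nil when weaning starts, f is near 0 and nothing is lost. With ρ = 0.7 and f = 0, change would even have more power than the level (96% against 81%). This also stands. But the hypothesis places the effect along complementary feeding, which includes its start, so f = 0 cannot be presumed.

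A reader might go further and infer that the change outcome would favour BLW because those infants start lower. The documents do not support that. The Background's worry about early intake under BLW concerns energy, not FV, and the article at once says the evidence for it is weak. If spoon-fed infants start younger, they might have the lower first FV record, which would push the other way. The earlier start under spoon-feeding is itself background literature; for this trial, timing is said only to depend on the participant.

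**Conclusion.** The concern holds in a limited form. The start-of-weaning record is post-exposure for maternal diet, is taken once the weaning method has begun, and has no fixed age. It is therefore not a valid baseline for either contrast, and an outcome labelled as change invites its use as one. The label also disagrees with the attainment proportion on which the 72 per group rests.

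For maternal diet, a literal change estimates D(1 − f), anywhere from the full effect to none. On the stated assumptions with ρ = 0.5, power falls from 81% at f = 0 to 30% at f = 0.5. The documents give no value for f. For the weaning contrast, the spans can differ by up to 2 months, but neither the size nor the direction of any bias can be derived. That both contrasts are biased in the planned analysis is not established, because that analysis can still be run on levels.

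**What to change.** Define the primary intake outcome as attainment of the FV recommendations, together with intake in g/day, at the fixed ages of 12 and 18 months. Compare groups on these levels (logistic model for attainment, the planned mixed model for g/day) with the child's age as the time axis. State that the effectiveness estimate is the group difference at those ages, not the interaction with time since the first record. The Sample size section gives no age for its 25% and 50%, so it should name the age to which they refer.

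Report the start-of-weaning record, with the age at which it was taken, as a descriptive post-exposure measure. Do not subtract it, and exclude it from the baseline covariates considered for adjustment. Do not use within-group tests of change as evidence of effectiveness.

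The cost is wording in the outcome and analysis sections. The same records are collected, and the sample size calculation then matches the outcome.
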